### Statistical methods

All data will be examined with regard to potential inconsistencies and missing values. Missing information in variables will be inspected and addressed by using multiple imputation methods [43], if appropriate. In order to check for systematic differences between completers and non-completers we will perform a dropout analysis. In addition, we will check if there are systematic differences between IG and active CG with regard to sociodemographic, health-related and employment variables. Analyses on primary and secondary outcomes will be performed as intention-to-treat. In addition, we will also perform a “per-protocol”-analysis including all participants from the IG that completed the goal agreement and their first intervention and participants from the active CG. Treatment effects on primary and secondary outcomes will be tested using appropriate panel-data regression models including group, time, an interaction between group and time as predictors and adjusting for relevant covariates and baseline outcome measures. Acceptability, uptake and adherence with regard to the intervention will be evaluated using descriptive statistics.

For all analyses the level of statistical significance will be set to *p* < .05. The results of the study will be reported according to the guidelines of *the Consolidated Standards of Reporting Trials* (*CONSORT*) statement [44].

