#### Active control group

Participants in the active CG will receive TAU and a booklet since a pure control group with no intervention would be neither feasible nor legally or ethically acceptable. The booklet gives an overview on current measures for vocational rehabilitation for individuals with mental illnesses.

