### Primary outcome

Our primary outcome is the proportion of participants “having worked at least one day in competitive employment” (yes vs. no) during the entire observation period upon t3 (18 months after baseline). We define competitive employment as employment that any person can apply for regardless of disability status. Workers earn minimum wage or higher, and self-employment is also considered to be competitive employment (also see ipsworks.org). It will be assessed as self-reported information via questionnaire.

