## Discussion

Our study is the first RCT in a German setting where the effects of IPS are tested with a broad group of individuals with severe mental illnesses receiving means tested benefits. We will analyses in how far the treatment affects the integration into the labor market as well as a wide set of vocational and mental health outcomes. The results of this RCT will fill a research gap, but they will also provide the scientific foundation for future measures to improve the reintegration and mental health of long-term unemployed persons with severe mental health problems. The demand for reintegration measures is already existing as a recent German study shows that two thirds of unemployed individuals with a severe mental illness exhibit a strong desire for work [45]. Our trial has several strengths and weaknesses.

One major strength is the fact that we are conducting an RCT, the gold standard in terms of methodology, and that participants are assessed at four points in time. Furthermore, we are assessing a wide variety of outcomes related to employment as well as mental health. This is important since an intervention as complex as IPS may affect a variety of outcomes. Furthermore, there is variation between IPS coachings, e.g. in terms of duration, which could have an effect on outcomes. We address this to some extent by additionally applying per protocol analysis with minimum requirements in terms of intervention attendance, and by rigorously documenting the process.

Another advantage of our study is the collaboration between three distinct actors, clinic, job center, and research institute, that includes project organization and staff training as well as communication and feedback, and a variety of other activities. The lessons learnt from this work can be used to further improve the collaboration in this area and to help create a more efficient and supportive environment for unemployed individuals with mental disorders. However, the COVID19 pandemic may challenge certain procedures and the subsequent labor market.

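### The supplementary per-protocol analysis selects on engagement in the intervention arm only, so it is not a randomised comparison and may favour IPS

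*Protocol article*

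**What the plan says.** The Statistical methods section makes intention-to-treat the analysis for the outcomes: "Analyses on primary and secondary outcomes will be performed as intention-to-treat". It then adds a per-protocol analysis "including all participants from the IG that completed the goal agreement and their first intervention and participants from the active CG". The CG part reads only "and participants from the active CG", with no attendance or engagement condition. None could correspond to the IG rule, because the control condition contains no coaching step: "Participants in the active CG will receive TAU and a booklet" (Active control group).

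Treatment effects are to be tested by regression, "adjusting for relevant covariates and baseline outcome measures". The covariates are not named, and one significance threshold (p below .05) is set for every analysis. Nothing in the text marks the per-protocol comparison as non-randomised or exploratory.

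The Discussion describes the role of this analysis. Coachings vary, for example in duration, and the authors respond to this in part by "additionally applying per protocol analysis with minimum requirements in terms of intervention attendance", together with documentation of the process.

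**The concern.** Completing a goal agreement and a first intervention happens after randomisation and can be observed only in the IG. The Intervention group section says the agreement follows a planning phase, that appointments may be missed, and that participants can withdraw at any time. People who do not get that far may be less motivated or less stable, and so less likely to work even one day "during the entire observation period upon t3 (18 months after baseline". The rule removes such people from the IG. Their counterparts in the CG cannot be identified and stay in the comparison.

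The per-protocol difference therefore mixes any effect of IPS with the difference between people who engage and everyone else. It would be reported with a p-value beside the intention-to-treat result, so a reader could take a larger per-protocol difference as evidence of what IPS achieves when taken up. It also does little about variation in coaching: a yes/no threshold at the first intervention does not measure duration or intensity.

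**Working it through.** **1. Reproducing the planning figure (Sample size).** Inputs: 0.55 versus 0.28, one-sided α = 0.05, power 0.80, mean rate 0.415. With the pooled-variance formula,

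n = [1.645·√(2·0.415·0.585) + 0.842·√(0.55·0.45 + 0.28·0.72)]² / 0.27² = (1.146 + 0.564)² / 0.0729 ≈ 40.1, so 41 per arm.

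41 / 0.70 = 58.6, so 59, or roughly 60 per arm. Both stated figures reproduce and are not in dispute.

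**2. Inputs for the bias check.**
- No IPS effect; employment rate 0.28 in both arms (the planning CG rate).
- f = share of the IG not meeting the criterion. The protocol gives none; assumed 0.20 to 0.30.
- r = job rate among those non-completers. Not given; assumed 0.05 to 0.15.
- Arm sizes: 60 randomised, or 41 evaluable.

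**3. Formula.** The whole IG has rate 0.28, so the retained IG has rate (0.28 − f·r)/(1 − f). The CG stays at 0.28. The bias is the difference.

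**4. Results.** Rejection rates come from exact enumeration of two binomials with the one-sided pooled z-test at 5%. Retained IG versus CG is 48 v 60 and 42 v 60, or 33 v 41 and 29 v 41.

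| f | r | Retained IG rate | Bias (points) | Rejection, 60 per arm | Rejection, 41 per arm |
|---|---|---|---|---|---|
| 0.20 | 0.15 | (0.28 − 0.030)/0.8 = 0.3125 | +3.25 | 9.6% | 9% |
| 0.20 | 0.05 | (0.28 − 0.010)/0.8 = 0.3375 | +5.75 | 15.2% | 14% |
| 0.30 | 0.15 | (0.28 − 0.045)/0.7 = 0.336 | +5.6 | 15.4% | 14% |
| 0.30 | 0.05 | (0.28 − 0.015)/0.7 = 0.379 | +9.9 | 28.2% | 23% |

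At f = 0.40 the bias would be +8.7 (r = 0.15) to +15.3 points (r = 0.05).

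**5. Cases that do not favour IPS.**
- r = 0.25: (0.28 − 0.05)/0.8 = 0.2875 and (0.28 − 0.075)/0.7 = 0.293. Bias is about +1 point; one-sided rejection is 6-7%.
- r = 0.28: bias 0, rejection about 5%.
- r = 0.35: (0.28 − 0.07)/0.8 = 0.2625 and (0.28 − 0.105)/0.7 = 0.25. Bias is −1.75 and −3.0 points.

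**6. Sidedness.** The sample size is one-sided; the Statistical methods section gives no side. With a two-sided 5% test and 60 per arm, rejection in favour of IPS is 6-10% at f = 0.20 and 9-19% at f = 0.30, against a nominal 2.5%. With 41 per arm, total two-sided rejection is about 6-15%.

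**7. The alternative in the same scenarios.** With complete outcomes, the intention-to-treat difference is 0.28 − 0.28 = 0 whatever f and r are. A complier average effect, the intention-to-treat difference divided by IG uptake, is then 0/(1 − f) = 0.

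**The case against.** The strongest reply is that this analysis decides nothing. Intention-to-treat is the stated analysis for primary and secondary outcomes, and neither the hypothesis nor the sample size depends on the per-protocol set. That stands. A reader might infer that the trial's main conclusion is compromised, but the documents do not support this.

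A reader might also infer that the bias is known to favour IPS. Nothing in the protocol shows that completing the goal agreement predicts employment. Inclusion requires at least a moderate wish to work from everyone, which narrows differences in motivation. Someone who finds a job alone before completing the agreement would push the bias the other way. Covariate adjustment might also remove part of it. These points stand as limits on direction and size. They do not restore comparability, because the covariates are unnamed and cannot be relied on to capture engagement.

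A third inference would be that the Discussion presents this analysis as proof of effectiveness. It does not: it claims only to address variation in coaching in part, alongside process documentation.

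Finally, a complier analysis that defines uptake as a completed goal agreement would have a bias of its own. Coaching begins with needs assessment before goals are written down, and coaches pursue non-attenders for 8 weeks. People without an agreement may therefore have been coached, and dividing by the smaller uptake would inflate the effect if partial coaching helps. This objection is sound and shapes the remedy.

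**Conclusion.** The concern holds in a limited form. The per-protocol rule is fixed in the protocol itself, so this is not a detail left to an unseen analysis plan. It applies a post-randomisation filter to one arm, and the resulting comparison is non-randomised whatever the sign of the bias. A bias towards IPS is plausible, not established.

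The +3 to +10 points, and one-sided rejection of two to nearly six times the nominal 5%, rest on assumed non-completion and job rates and on an unadjusted test. They show that the bias could matter; they do not predict it. This is something that should be fixed, not a flaw in the primary result.

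**What to change.** - **Label the current subset.** Call it non-randomised and descriptive, and report it without a between-arm p-value.
- **Add a complier average causal effect** with randomised arm as instrument. For the primary outcome this is the intention-to-treat risk difference divided by the IG uptake proportion, with a bootstrap or two-stage confidence interval.
- **Define uptake as any IPS coaching contact**, so that it is plausible that allocation has no effect on those counted as not taking it up. Use goal agreement plus first intervention as a sensitivity analysis.
- **State the assumptions.** The booklet goes to the CG only, so the method also assumes that the booklet makes no difference to people who would never take up coaching. Concomitant care is unrestricted, so check whether any CG participant received IPS. If so, the denominator is the difference in uptake between arms.

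The cost is a change of wording. The coaching documentation already planned should supply the uptake variable. The price is a wider interval and reliance on the exclusion restriction. The change should be made before outcome data are seen by arm, since redefining the set afterwards would not be credible.

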**Methods:**

In this randomized controlled trial, about 120 eligible participants aged between 18 years and local retirement age will be randomly allocated to an intervention group (IG) or to an active control group (CG) using a parallel arm design. The IG will receive IPS + high quality treatment as usual (TAU), the active CG will receive TAU + a booklet on integration measures. A block-randomization algorithm with a targeted assignment ratio of 1:1 for participants in IG and active CG will be used, stratified by sex and three age groups. Assessments will take place before the intervention at baseline (t0), and 6 (t1), 12 (t2), and 18 (t3) months later. Primary outcome will be the proportion of participants having worked at least 1 day in competitive employment since baseline, as assessed at t3. Secondary outcomes will be related to employment/ vocation and mental health. In addition, there will be a process evaluation. Treatment effects on outcomes will be tested using appropriate panel-data regression models, and acceptability, uptake and adherence will be evaluated using descriptive statistics and appropriate inference testing.

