### Objectives

The objective of the LIPSY trial is to test the effectiveness of an IPS intervention in a German context, and with long-term unemployed individuals with severe mental illnesses that receive means-tested benefits. The intervention aims at maintaining or regaining their working ability and at facilitating their reintegration into the first labor market. We will test the hypothesis that IPS is superior to the treatment of the active control group (a booklet on integration measures). Specifically, we assume that participants will be significantly more likely to have worked in competitive employment for at least 1 day at t3 (18 months after intervention, primary outcome) if they received IPS (IG) as compared to not receiving IPS (CG). In addition, we will analyses the effects of the intervention on a wide range of vocational and health-related outcomes. Therefore, the present study closes a research gap in Germany, and if proven effective may further close a supply gap for reintegration of individuals with severe mental health problems.

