### Sample size

Sample size calculation is based on the primary outcome measure (competitive employment for at least 1 day). In the IPS-literature there is only one European Trial with data from a German study center [12]. The proportions of the EQOLISE-Trial were applied in the power calculation (IG: 0.55, CG: 0.28). To detect a between-group effect of ∆ = 0.27 in favor of IG at 18 months, considering a significance level of α = 0.05 (one-sided) and a statistical power of 1 - β = 0.80, we estimated a target sample of *n* = 41 participants per arm is needed. Anticipating a drop-out rate of 30% until 18 months after baseline assessment based on experiences with previous clinical research projects, the total sample size would have to comprise roughly 60 individuals per group.

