### Assignment of interventions: allocation and blinding

Eligible persons who consented to participate will be randomly assigned to either IG or active CG using a computerized random number generator. A block-randomization algorithm with a targeted assignment ratio of 1:1 for participants in IG or active CG will be used, stratified by sex and three age groups: 18–35, 36–50, 51+. This facilitates balance between study arms in both sample size and basic demographic variables. Stratified randomization will be achieved by using a separate randomization procedure within each of the strata.

Blinded randomization will be done by an independent statistician, generating randomization block lists with respective statistics software. The randomization lists (one for each stratum) will be concealed to the study coordinator and recruiting staff members with regard to the lists’ strata identity. Employees at job center and clinic who recruit eligible participants and collect data, will remain blind to the group allocation. Participants of both IG and active CG cannot be blinded to the intervention they receive, because blinding is per se not possible when conducting an IPS intervention. However, the statistician analyzing the data and staff members evaluating the results will remain blind to the group allocation.

An independent researcher will generate the allocation sequence. Psychologists from the clinic will enroll participants and inform the researchers about the enrollment who will then initiate randomization and assign the participants to one of the groups.

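### The protocol puts the primary outcome, a single cumulative yes/no value at 18 months, into a generic panel model and does not fix the 18-month contrast the trial was sized for

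*Protocol article*

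**What the plan says.** Four parts of the protocol article describe the primary outcome as one value per person at one time:

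- The Methods paragraph of the abstract: "having worked at least 1 day in competitive employment since baseline, as assessed at t3".
- Primary outcome: a yes/no item "during the entire observation period upon t3 (18 months after baseline").
- Objectives: IPS participants are expected to be "significantly more likely to have worked in competitive employment for at least 1 day at t3".
- Sample size: "To detect a between-group effect of ∆ = 0.27 in favor of IG at 18 months", with assumed proportions of 0.55 and 0.28, one-sided α of 0.05 and 80% power, giving 41 per arm and roughly 60 after 30% drop-out.

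The Statistical methods section then covers all outcomes in one sentence: "Treatment effects on primary and secondary outcomes will be tested using appropriate panel-data regression models including group, time, an interaction between group and time", and continues with "adjusting for relevant covariates and baseline outcome measures". It does not name the link function, say whether t0 is a response row, or say which coefficient or contrast is the confirmatory test. Randomisation is "stratified by sex and three age groups". The Secondary outcomes section has vocational items collected from t1 to t3, so cumulative employment status could be built at each follow-up, but the primary outcome is not defined that way.

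**The concern.** The stated model form does not match the outcome it is assigned to.

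1. A value that exists once per person has no time dimension, so time and group-by-time have no meaning for the primary outcome as defined.
2. Employment counted from baseline is 0 for every participant at t0, so there is no baseline value to adjust for.
3. If the outcome is rebuilt at t1, t2 and t3, the group-by-time term on the logit scale tests whether the log odds ratio changes between visits. The hypothesis asks whether more people have worked by month 18.

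One sentence therefore admits several tests. They answer different questions and have very different power. The choice could be made after the data are seen, and one plausible choice could miss an effect of the planned size.

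**Working it through.** **Step 1. Reproduce the sample size.** Inputs from the Sample size section: p1 = 0.55, p2 = 0.28, Δ = 0.27, mean 0.415, z(0.95) = 1.645, z(0.80) = 0.842.

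n = [1.645·√(2·0.415·0.585) + 0.842·√(0.55·0.45 + 0.28·0.72)]² / 0.27² = (1.146 + 0.564)² / 0.0729 = 40.1, rounded up to 41 per arm. This matches the plan. Drop-out: 41/0.70 = 58.6, i.e. 59, consistent with roughly 60. The trial is sized for one two-proportion comparison at t3.

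**Step 2. Power of that comparison with 41 per arm.** (0.27·√41 − 1.146)/0.670 = 0.87, so power is 80.8% one-sided. A Wald test of the log odds ratio gives 78.8%: estimate 1.145, SE = √[(1/0.2475 + 1/0.2016)/41] = 0.469, and Φ(1.145/0.469 − 1.645) = 0.79.

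**Step 3. Power if the group-by-time coefficient is the test.** The documents do not give the timing of job starts, so three paths were assumed, all ending at 0.55 and 0.28. For cumulative status at times s < t within an arm, cov(p_s, p_t) = p_s(1 − p_t)/n. On the logit scale, the variance of the change from t1 to t3 within an arm is

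[1/(p1(1−p1)) + 1/(p3(1−p3)) − 2/((1−p1)p3)]/n,

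where p1 and p3 are now that arm's proportions at t1 and t3.

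Constant hazards: t1 proportions are 0.234 and 0.104. The log odds ratio moves from 0.97 to 1.145, a change of 0.176. The bracket is 4.88 for IG and 7.75 for CG, so SE = √(12.63/41) = 0.555 and one-sided power = Φ(0.176/0.555 − 1.645) = 9%.

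| Assumed path (t1 IG vs CG) | Logit change, t3 minus t1 | One-sided / two-sided power, logit | One-sided / two-sided power, risk difference |
|---|---|---|---|
| Constant hazards (0.234 vs 0.104) | 0.176 | 9% / 6% | 44% / 32% |
| Early effect (0.35 vs 0.10) | −0.433 | 0.7% / 13% | 8% / 6% |
| Late effect (0.15 vs 0.10) | 0.683 | 29% / 20% | 73% / 62% |

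In the early path the logit interaction has the wrong sign for a one-sided test although the full 27-point difference is present at t3. A simulated GEE with linear time under constant hazards (600 runs, 41 per arm) gave 14% one-sided and 10% two-sided.

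**Step 4. Readings of the same sentence that keep the power.** In the same simulation, a panel model on t1 to t3 with categorical time and the group contrast taken at t3 rejected in 80.2% of runs one-sided, the same as a logistic model on t3 alone. In a linear probability model with t0 rows, the t3 interaction equals the raw t3 risk difference (0.415 for both in a simulated data set), so it tests the right quantity.

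**Step 5. Estimability.** As a covariate, the baseline outcome is constant: the design matrix with intercept, group and baseline outcome has rank 2 of 3. The term drops out and the group effect remains. With t0 rows in a logit model there is complete separation (standard errors of about 20,000 to 29,000), and the interaction cannot be estimated.

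**The case against.** The strongest reply is that the protocol does not name the interaction as the confirmatory coefficient. It lists predictors for models it calls appropriate, and its other sections all point to t3. Read together, they suggest a t3 group difference, and Step 4 shows that an ordinary panel model can deliver it with the planned power. This stands. A reader might infer that the confirmatory test is bound to be either almost without power or not estimable. The documents do not support that, because it holds only under particular choices of link, rows and coefficient that the text leaves open.

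The other replies also have some weight:

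- The baseline phrase makes sense for the secondary outcomes measured at t0. For the primary outcome it is void but harmless, since the term drops out.
- A reader might infer that covariates will be picked from the check of arm differences. The text does not link the two, and a list of covariates may properly sit in the analysis plan.
- A panel model may have been meant to use t1 and t2 reports from people who later drop out. That is a fair aim, but the outcome definition can meet it directly, because a job reported at t1 already makes the person a yes.

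It could also be said that an analysis plan, not shown here, settles the matter. The article, however, is not silent: it names the primary outcome and lists the model terms, and that list does not match its own outcome definition, hypothesis and sample size.

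**Conclusion.** The point holds in a limited form. The protocol assigns a generic longitudinal model to a single-time binary outcome, includes a baseline adjustment that is empty for that outcome, and does not fix the t3 contrast on which its 41 per arm rest. With 41 evaluable per arm, power is about 80% one-sided if the t3 contrast is tested, and about 1% to 29% one-sided (6% to 20% two-sided) if the logit group-by-time coefficient is tested. On the risk-difference scale the t3-minus-t1 interaction has 8% to 73% one-sided.

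The sample size result and the estimability results need no timing assumption. The interaction figures rest on the plan's proportions of 0.55 and 0.28 and on three assumed paths of job starts, so they show a range and are not a forecast. The mismatch concerns the confirmatory test and should be resolved before outcome data are examined.

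**What to change.** - State that the primary test is the between-group comparison of any competitive employment by t3. Use one binary regression per person on arm, sex and age group (the factors already used to stratify randomisation), with no time term and no baseline-outcome term. Report the standardised risk difference with its 95% CI.
- State that a job reported at t1 or t2 counts as a yes at t3 even if the t3 questionnaire is missing, and that the remaining missing t3 values are handled by the planned multiple imputation.
- Limit the panel model with group, time, group-by-time and baseline value to the outcomes measured repeatedly from t0 to t3: EQ-VAS, SF-12, PHQ-9, the symptom checklist scales, AUDIT-C and RTW-SE.

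The cost is a rewording of the Statistical methods paragraph. It needs no new data, no extra participants and no change to the sample size calculation. If the analysis plan already names the t3 comparison, only the protocol sentence needs to be aligned with it.
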